### Trial safety

2.12

The study team will give the subjects or their designated agents a complete and comprehensive introduction to the study objectives, study procedures, investigational drugs, reasonably expected benefits, possible toxicities, and the risks of participating. Written informed consent will be obtained from all subjects to protect their legitimate rights and interests. The study team must improve an emergency plan before the start of the trial. This will involve communication with multiple disciplines to inform them of the possible adverse events that may occur during this clinical study and to obtain their assistance in case of an emergency. The dose and concentration of S-ketamine that will be received by subjects in this trial were selected based on the pharmacokinetics, pharmacodynamics, published clinical trials, and recommendations from the drug’s manufacturer. Interventions for tachycardia, bradycardia, hypotension, and hypertension include adjustment of the study drug infusion, administration of vasoactive agents, or both. Interventions for hypoxemia include oxygen administration or physical therapy. Management of subjects with POD should first include identifying and correcting the underlying etiology, including the immediate exclusion of life-threatening causes such as hypoxia, hypotension, hypoglycemia, and sepsis. Non-pharmacologic treatment is the first-line treatment strategy. Haloperidol will be administered to subjects with severe agitation (RASS score of +3 or greater) who fail to respond to non-medical therapy. The study team will treat or rescue drug-induced adverse reactions such as nausea, vomiting, and anaphylactic shock according to established standard operating procedures. The investigators involved in this trial have extensive clinical experience, are good at handling acute and critical events, and have received professional Good Clinical Practices (GCP) training. The multifunction monitor will monitor the subject during the procedure and in the PACU. Subjects will be monitored continuously in the surgical ward for at least 24 h using ECG, blood oxygen levels, and blood pressure.

### Adverse events reporting

2.13

Adverse events (AE) refer to all untoward medical events that occur after the subject receives the investigational product. These include symptoms, signs, diseases, or laboratory abnormalities but may not necessarily have a causal relationship with the investigational product. The investigator should record and report all AE that are directly observed or spontaneously written by the subject in concise language. In addition, subjects should be asked about AE from the beginning to the end of the trial. AE should be recorded on the designated Adverse Event Form. The severity of AE will be judged according to standard adverse reaction evaluation criteria. All AE will be handled according to the standard operating procedures for handling adverse reactions that were developed by the clinical trial center. The AE record form shall be truthfully filled in, including the occurrence time, severity, duration, measures taken, and outcome of the AE.

A serious adverse event (SAE) refers to death or a life-threatening event, permanent or severe disability or loss of function, hospitalization or prolongation of hospitalization, a congenital anomaly or disability, or any other important medical events experienced by the subject after receiving the investigational product. Any subject with SAE should be withdrawn from the trial, and the investigator should actively treat the subject with SAE. The investigator must also complete the SAE Report Form in as much detail as possible, and sign and date it. The investigator should report the SAE to the Principal Investigator ([name]) and the Ethics Committee of Qingdao University within 24 h of being informed of the SAE.

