#### Delirium

1.1.1

Postoperative delirium (POD) is an acute, transient brain dysfunction that mostly occurs within 1 week of surgery. It is characterized by inattention, changes in consciousness level, and acute changes in cognitive function. The incidence of POD varies with patient population, type of surgery, and delirium assessment tools. Elderly patients are at a high risk of POD. The incidence of POD among patients aged 60 years and older is 12.0–23.8% (Silva et al., 2021). POD is independently associated with multiple adverse outcomes, including extended hospital stays, increased medical costs, and 30-day readmission rates. POD also increases perioperative and long-term mortality risk, increases the risk of dementia, and decreases cognitive function and health-related quality of life (Witlox et al., 2010; Kong et al., 2022). The pathogenesis of POD is complex. It may be caused by one (hypoxia, hypoglycemia, or cholinergic antagonism) or multiple neurobiological mechanisms. However, the vulnerability of the degenerative brain to acute stressors or precipitating factors is a key pathophysiological basis for the development of POD (Wilson et al., 2020). The degenerative brain can manifest as impaired brain network connections (Tijms et al., 2013), abnormal activation of glial cells (Hennessy et al., 2015), exaggerated neuroinflammation (Hennessy et al., 2015), and increased permeability of the blood–brain barrier (BBB; Sweeney et al., 2018), all of which are vital processes that contribute to vulnerability (Figure 1). The vulnerable degenerative brain is unable to quickly recover from acute stressors or precipitating factors. At the molecular and cellular levels, the mechanisms by which acute stressors or precipitating factors lead to POD include insufficient brain energy metabolism (Engel and Romano, 2004), neuroinflammation (Alam et al., 2018), neurotransmitter imbalance (Itil and Fink, 1966), changes in neuroanatomic integrity (van Montfort et al., 2019), and impaired neuronal network connectivity (van Montfort et al., 2019).

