#### Drop-out criteria

2.2.3

A subject may be withdrawn from the trial for the following reasons: (1) the investigator considers it necessary to stop the trial due to a medical ethics issue; (2) the incidence of a severe adverse event; (3) withdrawal from the study is felt by the investigator to be in the best interest of the subject; (4) poor compliance; (5) the subject has the right to withdraw from the trial midway through, or may not withdraw their informed consent but choose not to receive a study intervention. The reason for the subject’s withdrawal from the trial will be recorded on a “Withdrawal/Change of Status” form.

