### Statistical methods

2.16

To analyze the primary study outcome, we will use the ITT analysis set. The ITT analysis set is defined as all subjects who undergo randomization regardless of their intervention. Data processing and analysis will be performed using R version 4.3.0 and the Storm Statistical Platform.^1^ Continuous variables will be tested for normality using Shapiro–Wilk, with normal data expressed as mean ± SD, non-normal data as median and interquartile range, and categorical data as number of cases (n) and percentage (%). For demographic data, baseline characteristics, and intraoperative data, quantitative data between the two groups will be compared using a two-independent sample t-test or Mann–Whitney U test, and qualitative data will be compared using the chi-square test, continuous corrected chi-square test, or Fisher’s exact test. The primary outcome is a dichotomous measure, and the odds ratio (OR) and 95% confidence interval (CI) of the incidence of POD between the intervention and control groups will be calculated using a logistic regression model. This is a pragmatic study, and potential confounding variables may bias the degree of association between interventions and primary outcomes. The logistic regression model will therefore include demographics and baseline characteristics as covariates. We plan to build four different models. Model 1 will only include grouping factors and not control for confounding factors. The net OR and 95% CIs will be calculated. Model 2 will adjust for sex, age, ASA classification, comorbidities, and education level. Model 3 will adjust for electrolyte abnormalities, hypoproteinemia, and anemia based on Model 2. Model 4 will adjust for smoking, alcohol use, history of falls, vision or hearing abnormalities, preoperative dementia, depression, functional status, frailty, sleep disorders, and aCCI based on Model 3. Adjusted OR and 95% CIs will be calculated from Models 2, 3, and 4. We will perform a sensitivity analysis on the primary outcome to compare the effects of different analysis sets (ITT and PP) and statistical methods (modified Poisson regression and logistic regression) on the robustness of the primary outcome. The PP analysis set excludes subjects who did not meet our eligibility criteria or had incomplete adherence to the trial medication. Subgroup analyses will be performed for age, gender, dementia, depression, frailty, sleep disorders, vision or hearing abnormalities, and functional status, and interactions will be investigated.

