### Missing data

2.17

Missing data in the ITT analysis set will be handled using the multiple imputation method, with the number of imputations set to 5 and the maximum number of iterations set to 50. Continuous variables will be imputed using a predictive mean-matching model, and categorical variables will be imputed using a logistic regression model.

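### Mandatory withdrawal from the trial after any SAE makes 3-day delirium status informatively missing, and it conflicts with the protocol's own drop-out and safety follow-up text

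*Protocol article*

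**What the plan says.** All references are to the protocol article.

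- **Section 2.13 (Adverse events reporting):** "Any subject with SAE should be withdrawn from the trial". The withdrawal is from the trial, not only from study drug, and is not limited to drug-related events. The SAE definition in the same section includes "hospitalization or prolongation of hospitalization" and a catch-all for other important medical events.
- **Section 2.2.3 (Drop-out criteria):** "A subject may be withdrawn from the trial for the following reasons", and the second reason is "the incidence of a severe adverse event". Here withdrawal is discretionary and the trigger is severity, not seriousness. The fifth reason covers a subject who keeps consent in place but declines the intervention.
- **Section 2.11.1:** delirium (POD) is assessed twice daily to day 3. The last assessment stands in for missing data only after discharge or death.
- **Section 2.11.3 and Table 2:** adverse events are monitored for 24 h or until they resolve, complications are counted to 30 days, and safety outcomes are collected until discharge.
- **Section 2.16:** "The ITT analysis set is defined as all subjects who undergo randomization regardless of their intervention". Secondary outcomes use the per-protocol set only, which excludes incomplete adherence to trial medication.
- **Section 2.17:** "Missing data in the ITT analysis set will be handled using the multiple imputation method".

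No section says that delirium or other outcome assessments continue after withdrawal for an SAE.

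**The concern.** An intention-to-treat analysis needs more than a set that lists everyone randomized. It needs their outcomes. If an SAE ends a patient's participation on day 0, 1 or 2, the remaining delirium assessments are not done, and the reason is an event after randomization that may be related both to treatment and to delirium risk. The protocol supports the second link: section 2.12 names hypoxia, hypotension and sepsis among the causes to exclude in a delirious patient.

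Missing-at-random imputation would fill these outcomes mainly from patients who had no SAE. Adding SAE status to the imputation model would help little. Among patients with an early SAE, those with a known 3-day status would be essentially those already positive and those covered by the discharge-or-death rule.

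If SAE rates differ between arms, the arm with more SAEs loses more delirium events, and the comparison tilts towards that arm. An analysis plan cannot recover data that the protocol tells staff not to collect.

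**Working it through.** **1. The passages side by side.** Section 2.13 is mandatory and triggered by a serious event. Section 2.2.3 is discretionary and triggered by a severe event. A serious event need not be severe, and a severe one need not be serious, so the two rules select different patients as well as treating them differently. Follow-up to resolution, to 30 days and to discharge (section 2.11.3, Table 2) fits poorly with a patient who has left the trial.

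**2. The plan's own figure.** Section 2.3 gives 17% vs 7% and 166 per group. Alpha is 0.05 two-sided (section 2.16). Power is not stated, so 80% is assumed. With mean rate 0.12:

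n = [1.96·√(2·0.12·0.88) + 0.842·√(0.17·0.83 + 0.07·0.93)]² / 0.10² ≈ 165, against 166 stated.

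166/0.90 ≈ 185, against 186 stated. The figure reproduces. The 10% loss allowance covers lost numbers, not outcome-related loss.

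**3. Size of the distortion (illustration).** Assumptions, none of them in the documents:
- s = proportion of an arm with an SAE, and q = true 3-day POD risk in those patients;
- the 3-day status of every SAE patient is lost, then filled at the rate of the remaining patients in the same arm.

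With p the true POD rate in the arm, the estimated rate is p* = (p − s·q)/(1 − s).

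*(a) True rates 17% vs 7%, equal SAE rates, intervention q scaled by 7/17.* The true odds ratio (OR) is (0.07/0.93)/(0.17/0.83) = 0.367.

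| s, both arms | q, control | Control p* | S-ketamine p* | Risk difference | OR |
|---|---|---|---|---|---|
| 2% | 30% | 16.7% | 6.9% | 9.8 points | 0.368 |
| 5% | 30% | 16.3% | 6.7% | 9.6 points | 0.369 |
| 5% | 50% | 15.3% | 6.3% | 9.0 points | 0.372 |
| 10% | 50% | 13.3% | 5.5% | 7.8 points | 0.378 |

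Last row: (0.17 − 0.10·0.50)/0.90 = 0.133, and (0.07 − 0.10·0.206)/0.90 = 0.055.

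*(b) No true effect (12% in both arms), q = 50% in both arms, more SAEs on S-ketamine.*

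| s, control vs S-ketamine | Control p* | S-ketamine p* | Spurious difference | Spurious OR | Rejection rate at nominal 0.05 |
|---|---|---|---|---|---|
| 2% vs 5% | 11.2% | 10.0% | 1.2 points | 0.88 | about 0.07 |
| 5% vs 10% | 10.0% | 7.8% | 2.2 points | 0.76 | about 0.12 |
| 2% vs 10% | 11.2% | 7.8% | 3.4 points | 0.67 | about 0.21 |

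First row: (0.12 − 0.02·0.50)/0.98 = 0.112, and (0.12 − 0.05·0.50)/0.95 = 0.100. The rejection rates use a normal approximation with 186 per arm and ignore the extra variance from imputation. If S-ketamine had fewer SAEs, the direction would reverse.

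**The case against.** Five things can be said in favour of the plan.

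1. *The rule does not contradict the ITT analysis.* This stands. A reader might infer a formal contradiction, but the set still holds every randomized subject, section 2.6 keeps even unblinded subjects in it, and missing values are imputed. What suffers is the collection of outcomes.

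2. *Delirium that leads to an SAE is already counted.* This stands for the primary outcome. Section 1.1.1 says "POD is independently associated with multiple adverse outcomes, including extended hospital stays", and prolonged stay is an SAE criterion, so a reader might infer that delirious patients are removed from the primary outcome. But one positive 3D-CAM establishes POD (section 2.11.2), and an SAE after day 3 cannot change a 3-day endpoint. Only patients with an early SAE and no POD yet are exposed. Nor do the documents show that SAE patients are probably delirious: they give no POD rate for them.

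3. *Withdrawn may mean study drug only.* The discretionary wording of section 2.2.3 and the continuing safety follow-up leave room for this. Against it, section 2.13 says the trial, and section 2.2.3 lists declining the intervention with consent intact as a ground for leaving the trial. The text does not settle the question, and that is itself a defect.

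4. *The size is all assumption.* This stands. With equal SAE rates the OR barely moves, and the larger distortions need markedly unequal rates. For scale, the standard error of the risk difference at 12% and 186 per arm is √(2·0.12·0.88/186) ≈ 3.4 points, so only the most extreme scenario is that large. The illustration also treats every SAE as early and before any POD, so it lies at the upper end for the rates assumed.

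5. *Secondary outcomes would lose these patients anyway.* Largely so. A patient whose 48 h infusion stops after an SAE may fall out of the per-protocol set whatever section 2.13 says.

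**Conclusion.** The point holds in a limited form. Section 2.13 conflicts with section 2.2.3 on whether withdrawal is mandatory and on what triggers it, and it fits poorly with section 2.11.3 and Table 2. Followed as written, it makes the 3-day POD status of patients with an early SAE and no POD yet missing for reasons related to outcome and possibly to treatment. Neither multiple imputation under missing-at-random nor the discharge-or-death rule corrects that.

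The size cannot be derived from the documents. On the stated assumptions, equal SAE rates of 2-10% mainly cost risk difference (10.0 down to 9.8-7.8 points), while an excess of SAEs on S-ketamine could produce a spurious OR between 0.88 and 0.67 with no true effect. The case for acting is that the bias is avoidable at little cost, not that it is known to be large.

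**What to change.** Reconcile sections 2.2.3, 2.11.3, 2.13 and Table 2 so that they give one rule and one trigger. Separate stopping study drug, a decision left to the investigators as it is now, from ending follow-up. State that after an SAE or stopping of study drug, the scheduled delirium, secondary and safety assessments continue and enter the ITT analysis, unless the patient withdraws consent or an ethics or best-interest ground in section 2.2.3 requires follow-up to end.

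The cost is a few sentences plus the ethics re-approval that section 2.19 requires for any amendment. The delirium assessments run only to day 3, when most patients should still be in hospital, so little work is added.

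This change alone does not return these patients to the secondary analyses. The per-protocol-only rule in section 2.16 would still exclude those with incomplete adherence and needs its own decision.

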### Data collection

2.14

Data will be collected via face-to-face interviews with subjects and relatives or extracted from the HIS (Table 2).

**Table 2 tab2:** Enrollment schedule, interventions, and assessments.

Outcome measure	Visit 1	Visit 2	Visit3	Visit4	Visit 5	Visit 6	Visit 7	Visit 8
Time	Day of admission	1 day pre-surgery	During operation	6 h post-operative	1 d post-operative	2 d post-operative	3 d post-operative	Hospital discharge
Eligibility screening	X		–	–	–	–	–	–
Informed consent	X		–	–	–	–	–	–
Demographic characteristics	–	X	–	–	–	–	–	–
Baseline measures	–	X	X	–	–	–	–	–
Randomization	X	–	–	–	–	–	–	–
Intervention	Intraoperative S-ketamine will be infused continuously at 0.20 mg/kg/h for 1 h, followed by 0.01 mg/kg/h for 48 h							
Incidence of POD	–	–	–	X	X	X	X	–
Onset time of POD	–	–	–	X	X	X	X	–
Duration of POD	–	–	–	X	X	X	X	X
Severity of POD	–	–	–	X	X	X	X	–
Subtypes of POD	–	–	–	X	X	X	X	–
NRS	–	–	–	–	X	X	X	–
Opioid consumption	–	–	–	–	X	X	–	–
Pump compression	Within 24 h of surgery							
Clinical outcomes	–	X	–	–	–	–	X	–
Length of stay	–	–	–	–	–	–	–	X
Safety outcomes	Throughout the study period until discharge							

POD, postoperative delirium; NRS, number rating score.

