#### Exclusion criteria

2.2.2

This trial is a pragmatic study, so exclusion criteria will not be strictly defined. This means that patients with preoperative dementia and depression will not be excluded. However, we plan to exclude: (1) patients who are delirious and psychotic before the start of the trial; (2) patients with contraindications to S-ketamine (such as allergies, intracranial aneurysms, hyperthyroidism, and glaucoma); (3) patients with severe cardiovascular disease (e.g., hypertension grade III, unstable angina pectoris, severe valvular heart disease, severe arrhythmia, severe macrovascular disease); (4) patients with severe hepatic or renal insufficiency (such as Child-Pugh score III, creatinine clearance rate < 35 mL/min); (5) patients with a substance abuse history (such as ketamine, cocaine, heroin, amphetamine, and methamphetamine); (6) patients taking psychotropic drugs (such as chlorpromazine, clozapine, olanzapine, risperidone, and quetiapine); (7) family history of malignant hyperthermia or patients at high risk for malignant hyperthermia (such as strabismus and scoliosis); (8) body mass index (BMI) ≤ 18 kg/m^2^ or > 30 kg/m^2^.

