### Baseline assessment

2.7

This is a pragmatic clinical trial, so we will identify confounding factors that may impact the primary outcome. The study team ([name], [name]) will visit the patient before surgery and perform a health assessment. The study team will document the subject’s baseline characteristics by consulting the Hospital Information System and via face-to-face interviews. Baseline characteristics that will be collected include the subject’s age, sex, American Society of Anesthesiologists (ASA) physical status classification system (I [healthy], II [mild systemic disease], III [serious systemic disease], and IV [serious systemic disease with persistent life-threatening condition]); BMI, education level (<elementary school, elementary school, and ≥ secondary school), comorbidities (cardiovascular system, central nervous system, respiratory system, urinary system, gastrointestinal system, and hematologic system), electrolyte level (any concentration of potassium, sodium, calcium and magnesium ions above or below the normal range is defined as abnormal), albumin and hemoglobin concentration, smoking status (smoking is defined as continuous or cumulative smoking for more than 6 months or smoking at least 1 cigarette per day and currently smoking. Subjects will otherwise be defined as never smoking), alcohol consumption (alcohol consumption is defined as an average of more than 60 grams of pure alcohol per day for men and more than 40 grams of pure alcohol per day for women), history of falls (falls within the past 6 months), the presence of vision or hearing abnormalities, preoperative pain scores at rest and exercise, and baseline measurements of mental state, attention, thinking, and consciousness levels using the Chinese version of 3D-CAM.

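### Table 2 randomises on the day of admission, before the baseline 3D-CAM and the operation, so the all-randomised primary set may hold patients who are never operated on

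*Protocol article*

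**What the plan says.** Table 2 (section 2.14) sets out the first three visits as "Day of admission 1 day pre-surgery During operation". Randomisation is marked once, at Visit 1 ("Randomization X"), with dashes at every later visit. Baseline measures are not marked at Visit 1 and appear at Visits 2 and 3: "Baseline measures – X X". Screening is marked at the same visit as randomisation: "Eligibility screening X".

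Section 2.7 includes in the preoperative assessment "baseline measurements of mental state, attention, thinking, and consciousness levels using the Chinese version of 3D-CAM". Section 2.2.2 excludes "patients who are delirious and psychotic before the start of the trial", without tying that moment to a visit. Section 2.2.1 makes hip or knee arthroplasty under intraspinal anaesthesia an inclusion criterion.

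Section 2.5 has a quality controller open the envelopes in enrolment order before the trial starts, and names no day. Table 2 is thus the only text that dates randomisation.

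Section 2.16 defines the ITT set, used for the primary outcome, as "all subjects who undergo randomization regardless of their intervention". Subjects who fail the eligibility criteria are removed only from the per-protocol set. Section 2.17 multiply imputes missing data in the ITT set. Section 2.11.1 has one further rule, which carries the last delirium assessment forward when a subject is discharged or dies within 3 days.

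**The concern.** Between admission and the operation a patient can become delirious, have surgery cancelled, or receive a different anaesthetic. If allocation has already happened, that patient belongs to the primary set by definition.

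The never-operated patient is the awkward case. Postoperative delirium is undefined without an operation. The carry-forward rule has no postoperative assessment to use, so the general imputation rule would fill in the outcome. The analysis would then contain invented values for an event that could not occur.

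The early date also gains nothing that the protocol describes. Study drug is first given during the operation (2.6, 2.9), and the drug administrator prepares syringes and pump according to each subject's allocation. No step between admission and surgery needs the allocation to be known.

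**Working it through.** **Order of events.** Visit 1: screening, consent, randomisation. Visit 2: demographics and baseline measures, including the 3D-CAM. Visit 3: operation under intraspinal anaesthesia and first study drug. Allocation precedes both the recorded delirium baseline and the procedure that defines the population.

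**The plan's own figure.** Inputs from section 2.3: 17% vs 7%, 1:1, 166 per group, 186 after a 10% allowance for loss to follow-up. Two-sided 5% comes from 2.16. Power is not stated, and 80% is assumed because it reproduces the figure:

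- n = 2 × 0.12 × 0.88 × (1.960 + 0.842)² / 0.10² = 165.8, so 166 per group.
- 166 / 0.9 = 184.4, so 185, against 186 stated. The difference is trivial.

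The sample size is therefore not in dispute.

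**Effect of the affected patients.** Let f be the share of those randomised who are affected. The protocol gives no value, so f = 3%, 5% and 10% are assumptions (about 11, 19 and 37 of 372). Power is the exact binomial probability that the pooled z test exceeds 1.96 in absolute value, summed over all outcome pairs.

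- *Lost:* n = 186 × (1 − f) per arm, rates unchanged at 17% and 7%.
- *Kept at control risk, no effect:* n = 186, intervention rate = 0.07(1 − f) + 0.17f, control rate 17%.

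| f | n per arm if lost | Power if lost | Intervention rate if kept | Risk difference | Power if kept |
|---|---|---|---|---|---|
| 0 | 186 | 85.7% | 7.0% | 10.0 points | 85.7% |
| 3% | 180 | 84.6% | 7.3% | 9.7 points | 83.0% |
| 5% | 177 | 83.9% | 7.5% | 9.5 points | 81.1% |
| 10% | 167 | 82.0% | 8.0% | 9.0 points | 75.8% |

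Counting the affected patients as having no delirium in both arms falls between the two columns (83.7% at f = 5%).

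**If the 10% allowance is already used up by ordinary loss.** At 166 per arm, exact power is 81.8% with f = 0. With affected patients kept at the control risk, it is 78.8%, 76.7% and 71.1% for 3%, 5% and 10%.

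**Which column applies.** If the imputation model contains the treatment arm, imputed outcomes follow each arm's observed risk. The contrast is then not diluted and the lost-information column is the closer guide. The last column needs patients who receive no study drug but have an outcome at the control risk. That does not describe a cancelled patient, and the protocol does not say that a patient given another anaesthetic would go without study drug.

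**The case against.** The strongest counter-argument is that patients are not randomised unscreened. Eligibility screening sits at Visit 1 beside randomisation, current delirium is one of the criteria it should cover, and the Visit 2 3D-CAM is listed as a baseline characteristic, not as an eligibility gate. This stands. The protocol does not say that delirium goes unchecked until Visit 2. But admission screening cannot detect delirium that begins later, a later cancellation, or a change of anaesthetic. The Visit 2 cells for screening and consent are blank, not dashed, and may be a merged cell; the extracted text cannot settle that.

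It can also be said that section 2.5 leaves room for the Visit 1 mark to mean number assignment, with the envelope opened later. That is possible, but section 2.5 names no day, so it does not displace the only date the protocol gives.

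Several stronger readings are tempting and are not supported:

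- A reader might infer that the primary set is bound to contain ineligible or never-operated patients. No cancellation, conversion or incident-delirium rate is given, nor the interval from admission to surgery.
- A reader might infer that the later cognitive and mood tests bring in ineligible patients. Section 2.2.2 states that dementia and depression are not exclusions.
- A reader might infer that covariates measured after allocation bias the adjusted models. Assessors are blinded (2.6), the envelope opener has no other role (2.5), and no study drug is given before surgery, so no mechanism is shown.
- A reader might see improper exclusions after randomisation. The primary set excludes nobody, and removing ineligible subjects is the ordinary function of a per-protocol set.
- A reader might take 75.8% as the expected power. It needs 10% of patients wholly untreated with outcomes at the control risk; if they are simply lost, power stays above 80% at every rate examined from 186 per arm.

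**Conclusion.** The point holds as a weakness in the order of events. Table 2 allocates before the recorded baseline 3D-CAM and before the operation. With an all-randomised primary set and multiple imputation, a patient who never has surgery would be given an imputed postoperative delirium outcome.

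The harm is lost information or dilution, with no bias shown. For an assumed 3% to 10% of those randomised, the loss from 85.7% power is about 1 to 4 points if the patients are lost, and about 3 to 10 points if they stay in untreated at the control risk. These figures rest on the plan's 17% and 7%, on the assumed rates, and on no other loss from 186 per arm. If ordinary loss already brings the arms to 166, even 3% kept without effect takes power below 80%.

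**What to change.** Open the next envelope after the Visit 2 assessments and confirmed eligibility, as close as practical to study-drug preparation on the day of surgery. Move the randomisation mark in Table 2 to match, and replace the undated wording in section 2.5 with that time point. This prevents most of the cases, whereas a rule in the analysis plan could only handle them once they had arisen. For the few that remain, state how a randomised patient with no operation enters the primary analysis, so that an outcome that cannot exist is not imputed by default.

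The documentary change is one table row and a sentence or two of procedure. The practical cost is that the quality controller, who opens the envelopes and has no other trial role, must be available near the time of surgery instead of at admission.
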